### Hypotheses

In line with earlier studies, active sentences uttered in response to complex visual scenes are assumed to be produced less rather than more incrementally [15, 32, 35, 65, 76]. Oppermann et al. [76] show for German that sentences with a frequent subject-verb-object ordering (e.g., ‘Die Maus frisst den Käse’, ‘The mouse is eating the cheese’) can be successfully planned in full even at the phonological planning stage. For English, Ferreira and Swets [35] similarly demonstrate that speakers plan their active sentences non-incrementally when no time constraint is imposed. Therefore, this study of Estonian assumes that the conceptual planning under low cognitive load is only weakly incremental or even non-incremental, but it is expected to become more incremental when additional cognitive load is imposed, i.e., under high cognitive load. In other words, if conceptual planning processes share resources with WM, then the detrimental effect of high cognitive load should show increase in the incrementality of conceptual planning. The effect of cognitive load on the incrementality should be observable in the increased proportional duration of the naming gaze at the actor first mentioned before the onset of speech.

As argued in the previous paragraph, sentence planning is expected to proceed weakly incrementally or even non-incrementally under low cognitive load. Accordingly, tonal variation is expected to be determined by the number of concepts maintained in the WM or by sentence length such that sentence-initial intonation peaks are higher in longer than shorter sentences. The high cognitive load and the incrementality of planning are predicted to be tightly interrelated with the advance planning of sentence intonation. First, the incrementality is expected to relate to low pitch peaks because the highly incremental conceptualization processes only foresee mentioning the first concept in subsequent utterances. Second, the cognitive load is predicted to increase the sentence-initial pitch peaks given that the mental load arising from maintaining a complex conceptual network in WM (as it may occur whilst planning long but not short sentences) is comparable to the mental load that emerges from memorizing a word list. Consequently, two different outcomes of the load manipulation on sentence-initial intonation peaks are possible (see Fig 1).

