**Fig 1 pone.0259343.g001:**
[figure not shown]
Illustration of hypotheses regarding sentence-initial intonation peaks based on the invented data. Error bars indicate the 95% confidence intervals.

First, regardless of sentence length, the pitch peaks could decrease to a level lower than the pitch peaks in short sentences under the low cognitive load. In this scenario, the high cognitive load affects short as well as long sentences, and the effect of high cognitive load is greater on long sentences than short sentences. Second, the effects of incrementality and the high cognitive load could accumulate such that, regardless of sentence length, the pitch peaks under the high cognitive load are about the same height as the pitch peaks in the short sentences under the low cognitive load. This scenario predicts the high cognitive load to affect the pitch peaks in long sentences but not short sentences.

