The first analysis tests the extent to which the proposed verb probe task tapped the conceptual retention. The proportional duration of naming gazes at the first-mentioned actors is assumed to increase under the high cognitive load. Thus, only the main effect of cognitive load is expected in this analysis. The second analysis investigates the absolute duration of naming gazes, as the interference effect may arise at the phonological planning stage (or semantico-syntactic encoding) instead. In particular, if the phonological encoding of the first-mentioned actors is disrupted due to the memorization of three words the duration of naming gazes right before the speech onsets should increase under the high cognitive load.

The third analysis checks the preliminaries of advance planning of sentence intonation. Namely, the aim is to test how constant the sentence-final low F0 is in the elicited sentences. For this, the statistical evaluation should find no effect of Sentence Length. Nevertheless, the sentence-final low F0 may increase under the high cognitive load, as the existing studies have reported generally higher and flatter F0 contours for speech under mentally challenging conditions [58–64].

Finally, the fourth analysis tests the effect of cognitive load on the scaling of sentence-initial pitch peaks. The significant interaction between Cognitive Load and Sentence Length should demonstrate that the degree of length-dependent pitch raise in sentence-initial pitch peaks depends on the cognitive load. If the cognitive load causes sentence planning processes to proceed incrementally and the incrementality of planning processes mainly bears on the scaling of the pitch peaks, then the sentence-initial pitch peaks are lower under the high load than under the low load, and the difference between the high and low load is greater in long sentences than in short sentences. If the incrementality and the high load both play a role in pitch scaling, then the tonal difference between the high and low cognitive load is expected to occur only in long sentences.

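### The rule for reading the pitch-peak result assumes that two opposing effects of load roughly cancel in short sentences; the plan does not establish this, so the pattern cannot separate the two mechanisms

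*Protocol article*

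**What the plan says.** The Hypotheses section of the protocol article names two routes from high load to pitch. Through planning, "the incrementality is expected to relate to low pitch peaks", and high load is expected to make planning more incremental. Through the memory task itself, "the cognitive load is predicted to increase the sentence-initial pitch peaks". The article then states that "two different outcomes of the load manipulation on sentence-initial intonation peaks are possible".

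- **First outcome.** Peaks fall whatever the sentence length; "the high cognitive load affects short as well as long sentences", with the larger fall in long sentences.
- **Second outcome.** The two effects accumulate so that "the pitch peaks under the high cognitive load are about the same height as the pitch peaks in the short sentences" under low load. Load then changes long sentences only.

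The Statistical analysis section turns these outcomes into a reading rule for the fourth analysis. Lower peaks in both lengths, with a larger fall in long sentences, are what is expected if incrementality is *mainly* responsible. If incrementality and load both contribute, "then the tonal difference between the high and low cognitive load is expected to occur only in long sentences". The same section gives the goal of the analyses as deciding between incrementality acting independently and the two acting together.

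The pitch model contains Load, Length, their interaction, block and trial. It has no incrementality term.

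**The concern.** When one effect pushes peaks up and another pushes them down, the observed change shows only their sum. A flat result in short sentences is what two acting effects produce when they happen to be of similar size. It is not what they produce in general. The rule treats this special case as the signature of both mechanisms.

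At stake is the answer to the study's stated question. A fall in both lengths could be reported as incrementality working independently when the memory load also contributed. A rise in short sentences would meet a plan that has no reading for it. The Introduction, under the heading on prosody and cognitive load, cites studies in which mental challenge raised F0, so a rise is not far-fetched.

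**Working it through.** The document states no figure for this rule, so there is nothing to reproduce. The check is algebra on the four Load by Length cells.

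**Inputs, from Hypotheses and Statistical analysis**
- Incrementality lowers peaks by *a* in short and by *b* in long sentences, with *b* > *a*.
- Memory load raises peaks by *m*, taken as equal in both lengths. This equality is an assumption; the article does not state it.

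**Formulas (high minus low load)**
- Short: *m* − *a*
- Long: *m* − *b*
- Interaction: (*m* − *b*) − (*m* − *a*) = −(*b* − *a*)

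**Illustration** with *a* = 0.5 and *b* = 1.5 in arbitrary units:

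| *m* | Short | Long | Interaction | Reading under the plan |
|---|---|---|---|---|
| 0 | −0.5 | −1.5 | −1.0 | mainly incrementality |
| 0.25 | −0.25 | −1.25 | −1.0 | mainly incrementality, although *m* is half of *a* |
| 0.4 | −0.1 | −1.1 | −1.0 | mainly incrementality, although *m* is four-fifths of *a* |
| 0.5 | 0 | −1.0 | −1.0 | both |
| 0.75 | +0.25 | −0.75 | −1.0 | none listed |
| 1.0 | +0.5 | −0.5 | −1.0 | none listed |
| 2.0 | +1.5 | +0.5 | −1.0 | none listed |

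The interaction is −1.0 in every row because *m* cancels from it. It therefore cannot distinguish the rows.

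**Different mechanisms, identical cells**
- *m* = 0.25, *a* = 0.5, *b* = 1.5 gives short −0.25 and long −1.25. So does *m* = 0, *a* = 0.25, *b* = 1.25. Both effects act in the first case and only incrementality in the second.
- *m* = 0.5, *a* = 0.5, *b* = 1.5 gives short 0 and long −1.0. So does *m* = 0, *a* = 0, *b* = 1.0. The rule reads both cases as both effects acting, but in the second only incrementality acts.

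More data would not separate these pairs, because their expected values are equal.

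**Does the plan fix the size of *m* relative to *a*?** The only statement about size says that the load of a complex conceptual network, as in long sentences, "is comparable to the mental load that emerges from memorizing a word list". That ties *m* to the extra pitch of long over short sentences, not to *a*. Suppose load removes the length effect entirely, as the second outcome has it. The length effect is then *b* − *a*, which is 1.0 in the table, and setting *m* to that value gives the row *m* = 1.0: short sentences rise by 0.5 and long sentences fall by 0.5. Taken literally, the plan's own anchor leads to cancellation only if *a* also equals the length effect, which is not stated.

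**Do the other analyses help?** The gaze analysis can show that planning became more incremental, and the sentence-final F0 analysis can hint at a general rise under load. The article links neither to the reading of the peaks, and neither shows how much of the change in peaks each route caused.

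**The case against.** Four points on the other side have force.

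1. The protocol does not demand exact cancellation. It says high-load peaks "are about the same height as the pitch peaks in the short sentences under the low cognitive load". A reader might infer that the rule works only at a single point, *m* = *a*. The text does not support that; it implies a tolerance, although none is defined.
2. The rule says *mainly*. A reader might infer that a fall in both lengths is read as incrementality alone. The rule does not say so, and where *m* is below *a*, incrementality does outweigh load. What remains is that the stated goal is an either/or choice, sharper than *mainly*, and a net fall cannot settle it.
3. Near-cancellation has some theoretical basis. Suppose pitch rises linearly with the number of concepts held, and highly incremental planning holds one. In single-agent pictures the step from short to first-concept-only then equals the step from long to short, and a comparable *m* would be close to *a*. But linearity is not stated. The section describing the present study also says that pitch is not raised in short sentences, which can be read as making *a* small.
4. The formal test is the Load by Length interaction, and it stays valid for its own question whatever *m* and *a* are. Under the plan's directions, a rise in short sentences would also point towards load even though it is not listed.

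The first two points limit the wording of the criticism, the third makes cancellation possible but not established, and the fourth limits the damage to interpretation.

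**Conclusion.** The concern holds as a fault in interpretation. The load effect in short sentences is a net effect, and the plan reads it as if its sign and size revealed which effects are present. The rule can mislead in three ways: a fall in both lengths does not exclude a load contribution, a rise in short sentences has no listed reading, and a difference only in long sentences can arise from incrementality alone when *a* is near zero.

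This rests on the article's own directions of effect. The statement that the interaction carries no information on *m* also assumes an equal load rise in both lengths.

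A reader might go further and say that most combinations are misread, or put a percentage on it. The document supports neither: the sizes of *m*, *a* and *b* are not given, any share depends on arbitrary ranges for them, and the power statement under Participants covers main effects and the three-way interaction, not a load contrast within short sentences. The design, the model and the interaction test are unaffected. The point merits correction before data collection but does not undermine the study.

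**What to change.** In Hypotheses and in the Statistical analysis text for the fourth analysis:

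- Report the load effect within short sentences with its 95% CI, described as the net of the two effects. It can be obtained as a contrast from the planned model; the significance tests now named cover only main effects and the interaction.
- Give it three readings: negative (incrementality outweighs load), compatible with zero (the effects offset, or both are small), positive (load outweighs incrementality).
- Add the third outcome, short-sentence peaks higher under high than under low load, to the two now listed.
- State that none of these patterns excludes a contribution from the other effect.
- Drop the inference from lower peaks in both lengths to incrementality acting independently, and align the stated goal with this.

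The cost is rewording the hypotheses and one decision rule. Data collection, model and sample size do not change. The price is a slightly weaker claim: the study can say whether load changes the length effect and which effect dominates in short sentences, but not that only one is at work.

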#### Statistical analysis

The goal of the statistical analyses is to determine whether the scaling of sentence-initial pitch peaks in long sentences is affected by an independent effect of incrementality or by the simultaneous effects of incrementality and high mental load. As the manipulations of the factors Double Actor (agent vs patient) and Identity (same vs different) elicit short and long sentences (see in Materials), the combinations of these are reduced into a factor Sentence Length (short vs long) for the main analysis. Thus, the main analysis examines the effect of the interaction between Cognitive Load (low vs high) and Sentence Length (short vs long) on (i) the proportional duration of naming gazes at the first-mentioned actors, (ii) duration of naming gazes, (iii) the sentence-final pitch valleys, (iv) and the sentence-initial pitch peaks.

The four dependent variables (duration of naming gazes, proportional gaze durations, sentence-final F0 minima, sentence-initial F0 maxima) are modelled with separate linear mixed-effects regression analyses (LMER, as implemented in the *lme4* package in [82, 85]). All models include the interaction between Cognitive Load (low vs high) and Sentence Length (short vs long) as the fixed effect, the block and trial number as the covariate effects, and random intercepts and slopes for items and subjects. The analysis will be carried out using sum-to-zero coding of the fixed effects. To avoid the convergence issues, the models will be optimized following the procedures suggested in Bates et al. [82]. First, the continuous variables block and trial are centred and/or scaled for the statistical analyses. Second, the convergence tolerances are adjusted by applying an optimizing algorithm diverging from the standard test but which results in the converging model. Third, and only in case the previous measures do not yield the convergence of the model fit, the random effects structure will be simplified by removing the correlations term from the random effects structure. Finally, the significances of the model estimates are obtained with the help of the *lmerTest* package [86] in R [85]. The significances of the main effects and the interaction are determined at the threshold of p<0.05.

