The exploratory analyses inspect the three-way interaction between the factors Double Actor (agent vs patient), Identity (same vs different) and Load (low vs high) on (i) the proportional duration of naming gazes at the first-mentioned actors (ii) and the sentence-initial pitch peaks. The first exploratory analysis of naming gazes aims to determine whether the pictorial scenes combining the similar and differing event participants either in agent or patient role would induce planning increments differing and gradually increasing in size. Known from the studies relying on the grouping effect (though with moving displays), the chunk conceptualized and planned before the speech onset increases together with the more complex phrase structures [37, 38]. The second analysis will assess whether the length-dependent pitch raising depends on the syntactic position of the length variation (as in [4]). If a large number of sentences will be uttered with a break between the subject noun phrase and the verb phrase, the desired significant interaction with Identity (i.e., Sentence Length) and Cognitive Load might only occur when Double Actor corresponds to the agent. The models of the exploratory analyses and the significance testing will follow the same procedures as described for the main analyses.

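### The three-way term named for the exploratory gaze analysis does not address that analysis's stated aim, and no planned term tests the predicted ordering of the four scenes

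*Protocol article*

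**What the plan says.** The Statistical analysis section of the protocol article opens its exploratory part with one sentence that covers two analyses: "The exploratory analyses inspect the three-way interaction between the factors Double Actor (agent vs patient), Identity (same vs different) and Load (low vs high"). The outcomes are "the proportional duration of naming gazes at the first-mentioned actors (ii) and the sentence-initial pitch peaks".

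The two analyses then receive different aims.

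- **Gaze.** The question is whether scenes with similar or differing participants, in the agent or the patient role, "would induce planning increments differing and gradually increasing in size". The reason given is that "the chunk conceptualized and planned before the speech onset increases together with the more complex phrase structures". Neither statement refers to load.
- **Pitch.** The question is whether the length effect depends on syntactic position, so that "the desired significant interaction with Identity (i.e., Sentence Length) and Cognitive Load might only occur when Double Actor corresponds to the agent". Load is part of this question.

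For modelling and testing, the section says "The models of the exploratory analyses and the significance testing will follow the same procedures as described for the main analyses". Those procedures include "The analysis will be carried out using sum-to-zero coding of the fixed effects" and "The significances of the main effects and the interaction are determined at the threshold of p<0.05".

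**The concern.** One term has been assigned to two different questions. For pitch it fits: an Identity by Load interaction found at only one level of Double Actor is a three-way interaction. For gaze the question concerns the four Double Actor by Identity scenes, whereas the three-way term asks whether load changes the Double Actor by Identity interaction.

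If the named term is read as the answer to the gaze aim, both outcomes mislead. A non-significant result says nothing about whether planning increments differ between scenes. A significant one shows that load alters the two-by-two pattern, not that increments grow. The gaze aim also makes a claim about order, and the section gives neither a rank order of the four scenes nor a contrast that would test one.

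**Working it through.** The plan states no figure on this point, so there is none to reproduce. The check is algebra on the planned model, followed by rejection rates under stated assumptions.

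**Inputs from the protocol article.** Three two-level factors, fully crossed; 8 images in each of 8 conditions per participant (Design); 60 subjects from the power calculation (Participants); sum-to-zero coding and a 0.05 threshold (Statistical analysis).

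**Assumptions not in the article.** The residual SD, the size of the steps and the order of the scenes. Call the scene means m1 to m4, with Double Actor/Identity codes (-,-), (+,-), (-,+) and (+,+). This order gives Identity the larger step.

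**Step 1: coefficients with ±1 coding.**

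- Double Actor = [(m2 + m4)/2 - (m1 + m3)/2]/2
- Identity = [(m3 + m4)/2 - (m1 + m2)/2]/2
- Double Actor x Identity = (m1 - m2 - m3 + m4)/4
- Three-way = half the difference between high and low load in the Double Actor x Identity coefficient

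| Scene means | Double Actor | Identity | Double Actor x Identity | Three-way |
|---|---|---|---|---|
| 0, 1, 2, 3 under both loads | 0.5 | 1.0 | 0 | 0 |
| 0, 1, 2, 5 under both loads | 1.0 | 1.5 | 0.5 | 0 |
| 0, 1, 2, 3 under low load only | 0.25 | 0.5 | 0 | 0 |
| 0, 1, 2, 5 under low load only | 0.5 | 0.75 | 0.25 | -0.25 |

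A constant shift between loads changes none of these. The first two rows show that the three-way term is zero for a grading shared by both loads. The third shows that it can also be zero when the grading exists under low load only: the change then sits in Double Actor x Load (-0.25) and Identity x Load (-0.5). The fourth shows that the term does respond to some load-dependent gradings.

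**Step 2: simulated rejection rates.** 4,000 runs, 60 subjects, 8 images per cell, residual SD 1, subject intercept SD 0.3, subject slope SD 0.09, no item variance, by-subject contrast t-tests. Gradings are the same under both loads, in units of 0.15.

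| Grading | Double Actor | Identity | Double Actor x Identity | Three-way |
|---|---|---|---|---|
| 0, 1, 2, 3 (range 0.45) | 0.96 | 1.00 | 0.05 | 0.056 |
| 0, 1, 2, 5 (range 0.75) | 1.00 | 1.00 | 0.96 | 0.047 |

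**Step 3: a weaker grading, main effects against an ordered contrast.** Equal steps of 0.05 SD under both loads, 60 subjects, 8 trials per cell, trial SD 1, no random slopes or item variance, t-tests with 59 df.

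- SD of a subject's cell mean = 1/√8 = 0.354.
- A two-level factor compares 4 cells with 4 cells: SE = 0.354 x √(1/4 + 1/4)/√60 = 0.0323.
- Identity differs by two steps: 0.10/0.0323 = 3.10, power about 0.86.
- Double Actor differs by one step: 0.05/0.0323 = 1.55, power about 0.33.
- Linear contrast with weights -3, -1, 1, 3, averaged over load: value 10 x 0.05 = 0.50; SE = (0.354/√2) x √20/√60 = 0.144; 0.50/0.144 = 3.46, power about 0.93. A simulation of 10,000 datasets gave 0.924.
- Three-way term in the same simulation: 0.050. For steps of 0.08 and 0.10 it stayed at 0.052 and 0.051, while the linear contrast reached 0.9996 and 1.0.

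**The case against.** The strongest reply is that, in this article, the word interaction describes the fixed-effect structure of a model and not the only coefficient to be read. The main analyses are introduced as tests of the Cognitive Load by Sentence Length interaction. Yet the first is then interpreted through the main effect of load alone, and the third through the absence of a Sentence Length effect. The procedures carried over to the exploratory models test main effects as well as the interaction, and the power statement under Participants names the three main effects.

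This reply stands to a large extent. A reader might infer from the 5% rejection rate that a real grading would be missed about 95% of the time and reported as absent. The documents do not support that: Double Actor and Identity are in the same model and tested by the same procedure, and at least one of them would usually pick up the grading. Nor is the assumption that planning is alike in two-agent and two-patient scenes left unexamined, because Double Actor and its interactions bear on it directly.

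It could also be said that contrast detail belongs in a fuller plan. That would answer a complaint of omission. Here the article names a term for a stated aim, and the two do not match.

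The reply leaves two things open. No sentence ties the lower-order terms to the gaze aim, whereas the main analyses do say which term answers which question. And separate tests of two factors and their interaction show that scenes differ, not that increments grow along a stated order.

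**Conclusion.** The concern holds as a mismatch between the named term and the gaze aim, together with the lack of any test of ordering. That the three-way coefficient is zero for a grading shared by both loads is exact and does not depend on the assumed variances or steps. The power figures do depend on them. The 86% and 92% assume 60 subjects, trial SD 1, equal steps of 0.05 SD, a contrast matched to the true order and no slope or item variance, so they are illustrative and favourable to the contrast. They show that the ordered contrast gains little in detecting that something differs; its value is that it addresses the question asked. The severity is minor: the analysis is exploratory, no main conclusion rests on it, and the planned data and model can already answer the question.

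**What to change.** For the first exploratory analysis, name Double Actor, Identity and Double Actor x Identity, averaged over load, as the target, with a joint 3-df test of whether the scenes differ. Add one ordered contrast over the four scenes, with the order written down before data collection. State its sign too: under the article's own measure, a higher proportional naming gaze means more incremental planning, so larger increments predict lower values. Report the four scene means with the contrast, since a significant linear trend does not by itself show that every step increases. Keep the three-way term for whether load changes the scene pattern, and for the pitch analysis, where it fits.

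The cost is about two sentences and two contrasts on the model already planned, with no new data. The one real commitment is that the scene order must be chosen in advance and cannot be revised once the means are seen.
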